**FIGURE 1 epi470064-fig-0001:**
[figure not shown]
Main components of the 24/7 EEG SubQ solution (UNEEG medical). (A) The implant consists of a lead with three electrodes and a ceramic housing with the electronics. (B) The external device powers the implant and enables recording of the data. (C) The implant is implanted entirely subcutaneously. (D) The device attaches to the clothes via a plastic clip (C1) or a disc‐shaped magnet. (E) For recording, the wire and disc of the external device attach to the skin overlying the implant housing with a small adhesive patch. Once a day, the external device is attached to a tablet for charging and transferring the data via a cloud‐based solution to the healthcare professional (HCP).

Using the 24/7 EEG SubQ system, it is feasible to record EEG data reliably from home for up to 15 months.^22^, ^23^ Preliminary data suggest the device has recording characteristics similar to scalp EEG (for 2 bipolar channels),^24^ with signal quality showing high long‐term stability.^22^ Observational studies have suggested its utility for objective seizure counting, including the detection of temporal periodicities of seizure occurrence.^25^, ^26^ However, it remains uncertain whether this tool is of demonstrated added value when used prospectively, in the real world.

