### Objectives

1.2

The primary objectives for this study are to investigate whether 24/7 EEG SubQ, (1) is more informative than a participant‐reported seizure diary, (2) is feasible and acceptable to participants and clinicians, (3) reduces the impacts of epilepsy and improves quality of life, and (4) provides gains to the healthcare system when rolled out into the NHS.

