## STUDY PROCEDURES

3

During Visit 1, participants will complete baseline patient reported outcome measures (PROMs) and subsequently will undergo an online qualitative interview at baseline. Following this, they will be implanted with the 24/7 EEG SubQ by the local surgical team (Visit 2). The implant is inserted under local anesthesia in the pre‐auricular region in the subgaleal space on a predetermined side (i.e. right or left) and orientation based on the treating clinician's instruction. The electrodes can be positioned anywhere in the arc illustrated on the right of Figure 1 panel C, which allows a wide range of focal epilepsies to be included. We aim to position the electrodes where ictal EEG changes are likely to be detected based on previous electroclinical data. Any surgical specialty with expertise operating within the head and neck region is eligible to implant the 24/7 EEG SubQ. The participant is discharged after a two‐hour observation period with an implant ID card. Visit 3 occurs 10–14 days after implantation, when procedures for data collection will again be explained, and the participant will commence EEG data collection and begin keeping an electronic seizure diary (Helpilepsy; Neuroventis, Overijse, Belgium).^27^ During 6 months of data collection, participants will receive a minimum of monthly feedback regarding recorded EEG data from their treating clinician. They will repeat PROMs at 2 months (Visit 4) and 6 months (Visit 5) and an online qualitative interview prior to explantation after data collection is complete. The participant will then exit the study. Treating clinicians will complete standardized questionnaires assessing their experience using the 24/7 EEG SubQ during the study and after the participant's last visit. A treating clinician at each site will participate in a qualitative interview after the last participant at that site has had his/her final visit.

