Continuous 2 channel EEG data will be recorded from visit 3 to visit 5. To accommodate different local IT requirements, two data transfer configurations are possible whereby encrypted EEG data can either be stored within local hospital servers or stored within a third‐party cloud hosting service. The data pipeline for EEG is summarized in Figure 3. The participant will connect the external device daily via a USB cable to a tablet with a preinstalled application for data upload and recharging. Recorded EEG data will be automatically downloaded to the tablet, encrypted, and transferred via a cloud‐based data transfer application running in Microsoft Azure. The encrypted data in transit are pulled by an application (installed either at the servers of the local hospital IT network or in a 3rd‐party hosting service). Data are decrypted, stored, and made available to the investigators and treating clinicians in the UNEEG EpiSight Analyzer (EEG reading software).

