### Statistical analysis of primary outcome measures

4.1

The research team will review raw EEG data from 24/7 EEG SubQ to identify seizures as the ‘ground truth’. We will assess the improvement in accuracy of seizure documentation using AI‐driven algorithm with rapid expert review applied to 24/7 EEG SubQ data (‘24/7 EEG SubQ detected seizures’), compared to using self‐reported participant diary alone. We will estimate for each participant the Spearman correlation between monthly diary report and ground‐truth, and the Spearman correlation between monthly 24/7 EEG SubQ detected seizures and ground truth. We will test the hypothesis that, across the cohort, the correlation between 24/7 EEG SubQ detected seizures and ground truth is higher than between the diary and ground truth. We will also calculate for diary and 24/7 EEG SubQ detected seizures the sensitivity, specificity, false positive rate, positive predictive value, and negative predictive value, for seizure detection. We will report using Standards for the Reporting of Diagnostic accuracy studies (STARD) principles.^31^

Feasibility and acceptability will be assessed by the proportion of participants who continue in the study for >3 months of 24/7 EEG SubQ data collection.

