### Statistical analysis of secondary outcome measures

4.2

Clinical relevance, changes in the clinical management plan for the participant, degree of confidence level of investigators initiating a change in their participant's clinical management plan, based on the input from the EEG data recorded with 24/7 EEG SubQ Solution, will be assessed by questionnaires.

Participant's reaction to receiving feedback on EEG data recorded with 24/7 EEG SubQ will be captured using an average score on a 10‐point Likert scale (positive (10) to negative (1)).

Adherence, acceptability, and performance will be assessed by: (1) Proportion of total study time (wear time) during which 24/7 EEG SubQ data are collected; (2) Questionnaires; (3) Proportion of Device Deficiencies.

In order to assess quality of life we will assess change over time for average EQ‐5D‐5L scores at baseline, 2 months and 6 months, change over time for average Participant Weighted Quality of Life In Epilepsy (QOLIE‐31‐P) scores at baseline, 2‐months and 6 months, change over time for average Impact of epilepsy scores at baseline, 2‐months and 6 months, and change over time for average Perceived self‐mastery over epilepsy scores at baseline, 2‐months and 6 months.

Costs and health outcomes will be estimated over a lifetime time‐horizon in order to consider longer‐term health and economic implications. Results of analysis will be presented in terms of cost per quality‐adjusted life‐year (QALY) gained. Average Client Services Receipt Inventory (CSRI) scores will be assessed at 6 months.

In order to compare our cohort with similar controls without 24/7 EEG SubQ, we will utilize historical controls from a recently completed study,^32^ which included 198 participants in the Treatment As Usual arm with ≥10 seizures/year. These participants were recruited similarly and completed four outcome measures that we will use at baseline and 6 months and CSRI.

In addition to the above, adverse events will be recorded throughout the study.

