## DISCUSSION

6

Epilepsy is a multifaceted, common neurological disorder with a high burden of morbidity, mortality, and cost.^32^, ^33^, ^34^, ^35^, ^36^, ^37^, ^38^, ^39^, ^40^, ^41^ It is clear that poor seizure control with unexpected seizure occurrence results in a reduced quality of life for people with epilepsy and their families.^42^, ^43^ The development of a robust, accurate approach to seizure detection and recording is therefore of the utmost importance. Given the convenience of mobile devices, wearable technology, and the general desire of people with epilepsy for the integration of these advances into their healthcare,^41^, ^44^, ^45^, ^46^, ^47^ the study described here seems a logical next step. By enhancing the quality of information available to PWE, we may promote improved self‐management resulting in better self‐efficacy, adherence to treatment, and avoidance of seizure triggers.^48^, ^49^ In addition to this, we may also expedite impactful treatment decisions, which ordinarily could take multiple visits to the treating clinician.^50^, ^51^

Our study sets out to address a major issue in epilepsy management by pursuing alternative means of seizure monitoring to enable more reliably informed decision making. A particular strength of this study is the integration of the device into clinical practice without overly stringent inclusion criteria. This allows treating clinicians the freedom to make decisions based on their own interpretation of the solution's capabilities.

There are also some study limitations. Our sample size is small and may not be representative of the whole epilepsy population. Recruitment may prove challenging given the need for implantation and increased demands on the clinician. Clinicians will need to familiarize themselves with reviewing data, which could prove to be time consuming. If the AI‐driven algorithm provided by UNEEG proves to be inadequate from a clinician's perspective, the sheer amount of data analysis may not be feasible for busy clinicians. It also raises issues in the UK, where neurologists are not routinely EEG trained, which necessitates reliance on neurophysiologists, which is potentially quite complicated and labor intensive.

We will determine whether 24/7 EEG SubQ is feasible and acceptable to PWE and clinicians alike. REAL‐ASE hopes to establish new avenues to improve quality of life for PWE.

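### The feasibility measure stops at 3 months of a 6-month recording course, so participants who stop in months 4 to 6 are counted as continuing

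*Protocol article*

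**What the plan says.** Section 1.2 places feasibility and acceptability among the primary objectives: whether the system "is feasible and acceptable to participants and clinicians". Section 4.1, on the analysis of the primary outcomes, gives the measure: "Feasibility and acceptability will be assessed by the proportion of participants who continue in the study for >3 months". The sentence goes on to tie the period to recording, and its last part reads "who continue in the study for >3 months of 24/7 EEG SubQ data collection". It gives no target proportion, no reason for 3 months, and does not say whether the denominator is consented, implanted or recording participants.

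The planned course is longer. Section 3: "During 6 months of data collection, participants will receive a minimum of monthly feedback". Section 3.1: "Continuous 2 channel EEG data will be recorded from visit 3 to visit 5", with Visit 5 at 6 months. In Table 1, correlations A and B are likewise defined across the 6 months.

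Other measures lie close by. Section 4.2 assesses adherence, acceptability and performance together, by wear time ("Proportion of total study time (wear time) during which 24/7 EEG SubQ data are collected"), questionnaires and device deficiencies. Table 1 has a satisfaction form at 2 and 6 months under acceptability (objective 5) and wear time over 6 months under adherence (objective 6). It has no feasibility objective. The 3-month proportion appears neither there nor among primary outcomes A to E in section 4.

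**The concern.** The intervention under test is 6 months of recording, but the measure is settled at the midpoint. Someone who tires of the device in month 4 and someone who records to Visit 5 contribute equally to the numerator. Late discontinuation is one of the things a feasibility question about long-term recording should bring out, and this measure cannot register it.

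The cut is also modest beside the article's own background in section 1.1, which reports from earlier work that "it is feasible to record EEG data reliably from home for up to 15 months".

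At stake is the meaning of the conclusion promised in section 6, that the study will determine feasibility and acceptability. A high 3-month proportion would support feasibility of a 3-month course. It could be read as supporting the 6-month course that was actually planned.

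**Working it through.** **Nothing to reproduce.** Section 4.1 gives no target or expected proportion for this measure. The article's one power figure (section 2.4) concerns the correlations and does not bear on this point.

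**Step 1. Direction.** Let r3 be the proportion who record beyond 3 months and r6 the proportion still recording at 6 months, with the same denominator. Everyone in r6 is also in r3, so r3 ≥ r6. The difference, r3 − r6, is the share who stop in months 4 to 6. This needs no assumption about rates.

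**Step 2. Size.** From the article: N = 33 (section 2.1), cut at 3 months (section 4.1), course of 6 months (section 3). Assumed: a constant proportion m of those remaining stops each month, with m from 1% to 10%. Then r3 = (1 − m)^3, r6 = (1 − m)^6, and each is multiplied by 33.

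| m per month (assumed) | r3 | r6 | 33 × r3 | 33 × r6 | People who stop in months 4 to 6 |
|---|---|---|---|---|---|
| 1% | 0.970 | 0.941 | 32.0 | 31.1 | 1.0 |
| 2% | 0.941 | 0.886 | 31.1 | 29.2 | 1.8 |
| 3% | 0.913 | 0.833 | 30.1 | 27.5 | 2.6 |
| 5% | 0.857 | 0.735 | 28.3 | 24.3 | 4.0 |
| 8% | 0.779 | 0.606 | 25.7 | 20.0 | 5.7 |
| 10% | 0.729 | 0.531 | 24.1 | 17.5 | 6.5 |

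The last column is taken before rounding. In proportions, the gap runs from 0.970 − 0.941 = 0.029 (3 points) to 0.729 − 0.531 = 0.198 (20 points).

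**Step 3. Precision.** With 33 people any such proportion is imprecise. For example, 28/33 = 84.8% has an exact 95% interval of 68.1% to 94.9%. The figure therefore needs an interval whichever time point is used.

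**Step 4. Would wear time show the late stopping?** Partly. Over a fixed 6 months, full wear for 4 months and then none gives 4/6 = 67%. Steady wear of 67% to the end gives the same value. A low average signals a problem but does not separate stopping from partial wear. The denominator also matters. Table 1 uses 6 months. Section 4.2 uses total study time, which could be read as each person's own time in the study, and the person who stopped and left after 4 months would then score 4/4 = 100%.

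**The case against.** The best defence is that the 3-month proportion does not stand alone. Wear time over 6 months falls when someone stops in month 4, the satisfaction form is repeated at 6 months, and exit interviews are planned. For acceptability much of this stands, and late stopping would leave a trace. It does not carry over to feasibility, because section 4.2 assigns wear time and questionnaires to adherence, acceptability and performance and does not mention feasibility.

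Second, the size rests on assumed dropout. That is right: at 1% a month the gap is about one person. Only the direction is certain.

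Third, an article may leave the definition of adequate recording to the full protocol. That is fair, and the absence of a wear minimum is not a fault here in itself. The 3-month cut, by contrast, is stated in the article.

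Several stronger readings are tempting but not supported:

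- *People who stay enrolled without wearing the device count.* The sentence ties the period to SubQ data collection, so they do not clearly qualify. At most, very low wear might count if no minimum is defined elsewhere.
- *Those who pass 3 months are declared successes.* No success threshold is set; they are counted as continuing.
- *Clinicians are left out.* The 3-month proportion concerns participants only, and section 6 warns that "the sheer amount of data analysis may not be feasible for busy clinicians". But treating clinicians complete questionnaires, including at 2 and 6 months, and one per site is interviewed.
- *The result would add nothing to the known 15 months.* That figure is a maximum from earlier studies, and the article describes NHS use as untested.
- *The primary correlations require six complete months from everyone.* They are defined across the 6 months, with no completeness rule for the individual participant.

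**Conclusion.** The point holds in a limited form. The stated measure is fixed at half the planned course without a reason, it cannot register stopping in months 4 to 6, and it can only equal or exceed 6-month continuation. The likely gap is about 1 to 6.5 of 33 people, or 3 to 20 points, if dropout is constant at an assumed 1% to 10% a month. Other planned measures soften this for acceptability but not for feasibility.

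There is also an inconsistency to settle. Acceptability is measured by 3-month continuation in section 4.1, but by the satisfaction form in Table 1 and by wear time and questionnaires in section 4.2. The 3-month proportion sits under the primary outcome analysis without being listed as an outcome.

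A reader might infer that the trial cannot assess 6-month acceptability at all, or that a favourable finding is built in. The documents support neither reading. The change is worth making because it costs little and brings the feasibility measure into line with the course being tested.

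**What to change.** 1. Define the feasibility measure as the proportion of implanted participants, and separately of consented participants, who are still recording at Visit 5 (6 months), with a confidence interval. Define recording by a minimum wear time set before the data are examined.
2. Add time to permanent discontinuation of recording, with reasons.
3. Keep the proportion beyond 3 months as a descriptive figure.
4. State one definition of acceptability across section 4.1, section 4.2 and Table 1, and enter the feasibility measure in Table 1 and, if it is meant as primary, in section 4.

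The cost is mainly wording. Recording time is already in the EEG data, and the reason for stopping is a short entry if it is not already recorded. The real downside is that the reported figure may be less favourable.

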### Statistical analysis of secondary outcome measures

4.2

Clinical relevance, changes in the clinical management plan for the participant, degree of confidence level of investigators initiating a change in their participant's clinical management plan, based on the input from the EEG data recorded with 24/7 EEG SubQ Solution, will be assessed by questionnaires.

Participant's reaction to receiving feedback on EEG data recorded with 24/7 EEG SubQ will be captured using an average score on a 10‐point Likert scale (positive (10) to negative (1)).

Adherence, acceptability, and performance will be assessed by: (1) Proportion of total study time (wear time) during which 24/7 EEG SubQ data are collected; (2) Questionnaires; (3) Proportion of Device Deficiencies.

In order to assess quality of life we will assess change over time for average EQ‐5D‐5L scores at baseline, 2 months and 6 months, change over time for average Participant Weighted Quality of Life In Epilepsy (QOLIE‐31‐P) scores at baseline, 2‐months and 6 months, change over time for average Impact of epilepsy scores at baseline, 2‐months and 6 months, and change over time for average Perceived self‐mastery over epilepsy scores at baseline, 2‐months and 6 months.

Costs and health outcomes will be estimated over a lifetime time‐horizon in order to consider longer‐term health and economic implications. Results of analysis will be presented in terms of cost per quality‐adjusted life‐year (QALY) gained. Average Client Services Receipt Inventory (CSRI) scores will be assessed at 6 months.

In order to compare our cohort with similar controls without 24/7 EEG SubQ, we will utilize historical controls from a recently completed study,^32^ which included 198 participants in the Treatment As Usual arm with ≥10 seizures/year. These participants were recruited similarly and completed four outcome measures that we will use at baseline and 6 months and CSRI.

In addition to the above, adverse events will be recorded throughout the study.

### Statistical analysis methods

4.3

The accuracy of the two groups, i.e., (1) AI‐driven algorithm with rapid expert review applied to 24/7 EEG SubQ data vs. ground truth and (2) self‐reported participant diary vs. ground truth, will be compared in two ways: a correlation‐based comparison and an agreement‐based comparison. For the correlation‐based comparison, we will first estimate Spearman correlation coefficients for both groups to evaluate their monotonic relationship with the ground truth. To compare these relations between the two groups, we will use a Wilcoxon signed‐rank test. For the agreement‐based comparison, we will use the Bland–Altman method to allow us to calculate the mean difference and the limits of agreement to determine if one group consistently over‐r underestimates the ground truth compared to the other group.^33^

Questionnaire‐based data (see Table 1) will be assessed using different methods. For categorical data collected at three different time points (start, 2 months, and 6 months), the Chi‐squared test will be used to assess whether there are significant changes in the distribution of responses over time. Likert scale's and the CSRI will be assessed with descriptive statistics (e.g., mean, median, and frequency distributions) to summarize participant responses. For comparing the quality‐of‐life questionnaires (e.g., EQ‐5D, QOLIE‐31‐P) between the study cohort and historical controls, the Mann–Whitney U test will be used. Differences will be considered significant at *p* < 0.05.

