### Trial design

2.1

REAL‐ASE (Clinical Trials NCT06144047) is a prospective, non‐randomized, multicentre, interventional study that will be performed across UK neurology centres. A total of 33 adults with epilepsy, treated as part of their routine clinical care across the recruitment sites, will be enrolled.

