### Data collection

3.1

PROMs will be collected at Visits 1 (baseline), 4 (2 months), and 5 (6 months) via the electronic data capture system REDCap (see Table 1 for details).^28^ Use of REDCap forced responses to progress surveys and email prompts to review data will be utilized to ensure data completeness with both participants and investigators.

**TABLE 1 epi470064-tbl-0001:** Primary and secondary objectives with corresponding outcome measures.

Primary objective	Corresponding endpoint(s)/outcome variable(s)
To investigate the diagnostic accuracy of 24/7 EEG™ SubQ Solution	Within‐participant correlation between seizure counts per month estimated from rapid clinician review of annotated 24/7 EEG™ SubQ data and ‘ground truth’ EEG seizure occurrences per month (derived from expert research team review of 24/7 EEG™ SubQ EEG data), across the 6 months of the study (‘correlation A’). Within‐participant correlation between seizure counts per month from participant‐reported seizure diary and ‘ground truth’ EEG seizure occurrences per month (derived from expert research team review of 24/7 EEG™ SubQ EEG data), across the 6 months of the study (‘correlation B’). Average difference between ‘correlation A’ and ‘correlation B’, across participants. Average difference between the number of AI‐driven automated seizure detections produced by EpiSight software and seizure counts estimated from rapid clinician review of annotated 24/7 EEG™ SubQ data, across participants. Clinician rating on the question ‘Overall, after review of annotated 24/7 EEG™ SubQ data for all participants, how would you rate your rapid clinician review?’, i.e., average score on a 10‐point Likert scale (‘the AI‐driven algorithm is very accurate compared to my rapid review’ (10) to ‘the AI‐driven algorithm is very inaccurate compared to my rapid review’ (1))

Secondary objectives	Corresponding endpoint(s)/outcome variable(s)
2 To investigate the clinical relevance of 24/7 EEG™ SubQ Solution	Change over time for average HCP questionnaires ‘Communication’, ‘Insight’ & ‘Potential of 24/7 EEG™’ scores at baseline, 2 months and 6 months

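### Section 4.3 names a chi-squared test for categorical answers that the same participants give at three time points; with positive within-person correlation, p-values for those secondary items are too large and power is lost

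*Protocol article*

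**What the plan says.** Section 4.3 of the protocol article (Statistical analysis methods) sets the rule. For questionnaire answers that are categorical and recorded at the start and again after 2 and 6 months, it chooses chi-squared, and it states the purpose in these words: "test will be used to assess whether there are significant changes in the distribution of responses over time". The significance threshold in the same paragraph is p < 0.05.

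The respondents are the same people each time. Section 2.1 describes a single non-randomized cohort: "A total of 33 adults with epilepsy". Section 3 has them complete the patient-reported measures at Visit 1, and then: "They will repeat PROMs at 2 months (Visit 4) and 6 months (Visit 5"). Table 1 also places clinician questionnaires at those times ("scores at baseline, 2 months and 6 months").

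No matched test for categorical data is named. For the primary comparison, by contrast, section 4.3 names a Wilcoxon signed-rank test, which does respect pairing.

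**The concern.** Pearson's chi-squared test on a table of time point by response category assumes that every answer comes from a different person. Here 33 participants answering three times give up to 33 × 3 = 99 answers from 33 people. A person's answers tend to agree across visits, so the change between visits varies less than the test assumes. The test then measures the observed change against too large a variance.

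What is at stake is sensitivity. The study has no concurrent control and only 33 people, so within-person comparison is its main source of precision for change over time. A test that discards the pairing could return a non-significant result for a real shift, and that result could be read as no effect. Chi-squared is also the only inferential test that section 4.3 names for change over time within the cohort.

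**Working it through.** **The plan's own figure.** None is given for this analysis. The 85% power in section 2.4 concerns the primary correlation comparison and does not enter here.

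**Inputs.** n = 33 (section 2.1); three time points and a 5% threshold (section 4.3). The within-person correlation φ of a binary answer is not in the documents. It is assumed to be equal between all pairs of visits, with a main range of 0.2 to 0.5.

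**True size for a binary item.** Let the proportion answering yes be p at every visit (no real change).

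1. Each visit's observed proportion has variance p(1 − p)/n. Any two visits have covariance φp(1 − p)/n.
2. Differences between visits therefore vary in proportion to (1 − φ)p(1 − p)/n, whereas Pearson's statistic standardises by p(1 − p)/n.
3. So in large samples Pearson's statistic follows (1 − φ) times a chi-squared variable with 2 degrees of freedom.
4. The 5% critical value on 2 degrees of freedom is 5.991, and the upper tail of that distribution at x is exp(−x/2). The true size is exp(−2.996/(1 − φ)).

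| φ | 2.996/(1 − φ) | True size of nominal 5% test |
|---|---|---|
| 0 | 2.996 | 5.0% |
| 0.2 | 3.745 | 2.4% |
| 0.3 | 4.280 | 1.4% |
| 0.5 | 5.992 | 0.25% |

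**Check at n = 33.** Simulation with 20,000 replicates from a latent-normal model with no true change gave a chi-squared size of 5.5%, 2.7%, 1.2% and 0.27% at φ of 0, 0.19, 0.33 and 0.50. Cochran's Q stayed between 4.8% and 5.2% throughout. For a five-category item, the chi-squared size fell from 4.6% to 0.2% as the latent correlation rose from 0 to 0.9.

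**Power, for illustration only.** The documents give no expected change, so a shift of 40% to 55% to 65% is assumed for a binary item, with all visits complete.

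| φ (about) | Chi-squared | Cochran's Q |
|---|---|---|
| 0 | 43% | 41% |
| 0.19 | 41% | 50% |
| 0.33 | 40% | 59% |
| 0.49 | 36% | 70% |

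**With missing visits.** Cochran's Q uses only people with all three answers. If 20% to 30% lack the 6-month answer at random (assumed):

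- At φ about 0.49, Cochran's Q has 54% to 61% power against 30% to 33% for chi-squared.
- At φ about 0.33, it has 44% to 50% against 34% to 35%.
- At φ about 0.19 with 30% missing, the two are nearly equal, at 37% against 36%.

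**Which items the rule reaches.**

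- The outcomes that Table 1 places at baseline, 2 and 6 months are changes in averaged scores: the clinician Communication, Insight, Potential and Management scores, EQ-5D-5L, QOLIE-31-P, Impact of epilepsy and Self-Mastery.
- Likert and CSRI data are assigned to descriptive statistics in section 4.3.
- The plainly categorical items under objective 3 concern changes to the management plan. Two of them (A and C) ask about the past month, and none is shown as a start/2/6-month item.
- The satisfaction form is scored at 2 and 6 months only.

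The chi-squared rule therefore governs whatever categorical responses remain. The article does not list them, and they may be few.

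**The case against.** The strongest reply is that little depends on this sentence. The three-time-point endpoints in Table 1 are averaged scores, the outcomes concerned are secondary, and the error does not manufacture positive findings. All of that stands, and it limits the point without removing it: the article states a test for a defined kind of data, and that test does not fit data of that kind. This is a stated choice, not a detail left to an analysis plan.

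It can also be said that the name might loosely cover a matched test that uses a chi-squared reference distribution. The text does not say so, and an analyst following it would run Pearson's test.

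Three stronger readings are tempting, and the documents do not support them:

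- **That the study would report false improvements.** With positive within-person correlation, the error for participant items runs the other way.
- **That the quality-of-life results or the primary result are undermined.** The former are averaged scores; the latter uses a paired test.
- **That the same size and direction of error apply to clinician questionnaires.** The number of separate clinicians is not given. Where one clinician answers for several participants, a shift in that clinician's opinion moves several answers together, which can work against the conservative effect.

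A complaint that the test ignores the ordering of graded answers is also weak here. Likert items are only described, and no other ordered item is identified.

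**Conclusion.** The point holds in limited form and should be fixed, though it does not threaten the study's main result. For categorical participant items repeated at start, 2 and 6 months, the chi-squared test in section 4.3 assumes an independence that the design lacks. On a binary item its true size is about 2.4% at φ = 0.2 and 0.25% at φ = 0.5, against a nominal 5%. These sizes rest on an assumed, exchangeable within-person correlation; the conservative direction holds for any positive value. The power figures rest in addition on an assumed change and are illustrative. At zero correlation nothing is lost.

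**What to change.** In section 4.3, replace the chi-squared test for categorical data at three time points with a matched analysis, and list the items it applies to.

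- **Binary items:** Cochran's Q across the three times, with McNemar's test for pairwise contrasts.
- **Unordered items with more than two categories:** a marginal-homogeneity test.
- **Alternative for all items:** a GEE or mixed model (ordinal where the answers are ordered) with the respondent as cluster.
- **Clinician questionnaires:** cluster on clinician where one clinician answers for several participants.

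No new data are needed and the change is a few lines of text. It does carry a cost. Cochran's Q, and Friedman's test if used for ordered items, drop anyone with a missing visit. Section 4.1 makes continuation beyond 3 months a feasibility measure, so loss before month 6 is foreseeable. The gain shrinks with such loss unless the model-based version is used, which keeps respondents with a missing visit.
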